## Abstract

**Background:**

Preventive activities carried out in primary care have important variability that makes necessary to know which factors have an impact in order to establish future strategies for improvement. The present study has three objectives: 1) To describe the variability in the implementation of 7 preventive services (screening for smoking status, alcohol abuse, hypertension, hypercholesterolemia, obesity, influenza and tetanus immunization) and to determine their related factors; 2) To describe the degree of control of 5 identified health problems (smoking, alcohol abuse, hypertension, hypercholesterolemia and obesity); 3) To calculate intraclass correlation coefficients.

**Design:**

Multi-centered cross-sectional study of a randomised sample of primary health care teams from 3 regions of Spain designed to analyse variability and related factors of 7 selected preventive services in years 2006 and 2007. At the end of 2008, we will perform a cross-sectional study of a cohort of patients attended in 2006 or 2007 to asses the degree of control of 5 identified health problems. All subjects older than16 years assigned to a randomised sample of 22 computerized primary health care teams and attended during the study period are included in each region providing a sample with more than 850.000 subjects. The main outcome measures will be implementation of 7 preventive services and control of 5 identified health problems. Furthermore, there will be 3 levels of data collection: 1) Patient level (age, gender, morbidity, preventive services, attendance); 2) Health-care professional level (professional characteristics, years working at the team, workload); 3) Team level (characteristics, electronic clinical record system). Data will be transferred from electronic clinical records to a central database with prior encryption and dissociation of subject, professional and team identity. Global and regional analysis will be performed including standard analysis for primary health care teams and health-care professional level. Linear and logistic regression multilevel analysis adjusted for individual and cluster variables will also be performed. Variability in the number of preventive services implemented will be calculated with Poisson multilevel models. Team and health-care professional will be considered random effects. Intraclass correlation coefficients, standard error and variance components for the different outcome measures will be calculated.

## Background

The Spanish National Health Service (NHS) provides universal cover and is financed, essentially, by general taxes. The system is divided into primary and secondary care. Primary care (PC) is organized as a network of primary health care teams (PHCT) that behave as geographical and administrative units where PC services are planned, managed and provided for a population ranging from 5,000 to 25,000 citizens. The PHCT staff includes: general practitioners (GPs), paediatricians, nurses, social workers, dentists and ancillary staff. GPs care for individuals older than 14 years (except in rural areas where they look after all members of the local population) and paediatricians look after those between 0 and 14 or 16 years, depending on the region. These clinicians act as gate-keepers for the rest of the public health care system. The PHCT works usually in a single health care centre but in rural areas there may have other small offices.

Secondary care includes out-patient and in-patient hospital care and out-patient care in multi-disciplinary clinics.

The Spanish NHS has been strongly decentralized into 17 Autonomous Communities or regions that configure the Spanish State. Each of these regions has its own governmental structure which, among other responsibilities, provides health-care services to the population. There are minor differences between them with respect to structure and administration. For example, in Aragon and Navarra all services are provided by the State-funded regional service while in Catalonia, the provision of primary care services is offered by different providers (state and non-state funded) among which the Catalan Health Institute (ICS) manages almost 80% of all PHCT. According to latest census of the year 2002, Aragon had a population of 1,209,888 inhabitants while Navarra had 560,235 inhabitants and Catalonia 6,418,387.

### Preventive services in Primary Care

PC is the most accessible health-care level to the general population. In Spain, more than 95% of the population visit their GP at least once in every 5 years. No other health-care level is in a better position to evaluate the global health status of the individual and to decide when to act and what are the ideal measures to take in each specific situation [1].

There is an increasing evidence of the health benefits achieved from the implementation of preventive measures in normal clinical practice. In the last quarter of the century several groups of experts such as the Canadian Task Force on Periodic Health Examination in 1979 [2] and the US Task Force in 1980 [3,4] have published evidence-based recommendations regarding the relevance and the outcomes of the implementation of preventive interventions. Prestigious institutions such as WHO and the Royal College of General Practitioners [5] have highlighted the valuable role of health-care professionals within PCHTs in developing these services.

In Spain, the Spanish Society of Family and Community Medicine *[Sociedad Española de Medicina de Familia y Comunitaria; semFYC] *launched in 1988 the Preventive Activities and Health Promotion Program *[Programa de Actividades Preventivas y de Promoción de la Salud; PAPPS] *that have as main objective promoting the implementation of preventive and health promotion services in PC [6]. The EUROPREV (European Network for Prevention and Health Promotion in Family Medicine and General Practice) was created to extend and coordinate the experiences from this program and to promote preventive services at the European level.

In the period between 1989 and 2003 PAPPS program carried out biennial evaluations of a representative sample of patients attending the PHCTs participating in the program (671 PHCT since the beginning of the program). These evaluations have been the only evaluations of preventive services carried out nation-wide and provide information on the progress and effectiveness of the program over its 15 years of existence [7-9]. From the studies we know that the best-implemented group of preventive services is the minimum package of the adult sub-program which includes screening for hypertension, smoking status and alcohol consumption (done in 92.8% of patients), followed by a second group that includes anti-influenza vaccination, screening for hypercholesterolemia and obesity and anti-tetanus vaccination (done in more than 70% of patients) [8].

However, the progressive implementation of systematic evaluations of primary care performance promoted by the Autonomous health administrations and the progressive computerization of clinical records has brought-about a re-thinking of this evaluation model. The computerization of clinical records provides rich information based on individual data (not centre aggregated data) on a wider and more representative sample that avoids manual and voluntary recording of data. This allows a better study of the clinical practice variability (CPV) and its determining factors.

### Clinical practice variability in preventive services in Primary Care

In Spain, there have been few nation-wide population studies evaluating CPV in PC. This has been due, in part, to the lack of reliable information systems. These studies have often been performed at a hospital level because of the existence of minimum basic data sets (MBDS) provided on discharge from hospital. Nevertheless, from the existing evaluations, PAPPs studies [8,9] and other national [10-13]and international [14-16] studies it is clear that there are important difficulties with respect to the correct implementation of preventive services and health promotion interventions and there is a high variability in their implementation. There is extensive literature on factors related to prevention of specific diseases but less related to implementation of a combination of preventive services as routine clinical practice in PC that may have a profound effect on different diseases. These factors vary considerably, depending on the type of study, the country and type of preventable disease. There are different factors associated with the supply and demand of services that result in elevated variability between and within centres: patient-related factors (socio-demographic and clinical factors), health professional associated factors (specialty, training and professional competence, number of years working with the PHCT), team related factors (existence of specific registries, workload, frequency of doctors encounters, teaching centre) and other health-care provision system characteristics [12].

High CPV translates into problems of clinical effectiveness and social efficiency in health-care provision and, as such, is of concern to health-care providers and to Society in general [17,18]. An analysis of CPV is therefore essential in decision making in the health-care provision politics and prioritization in clinical management (e.g. to generate guidelines for implementation in those areas of high clinical variability).

Hence, it is essential to have studies that include a territory-wide sampling in order to achieve greater representativeness and which take into account methods of design and statistical analysis (e.g. cluster-based analyses) to obtain valid estimates and to explore the influence of patient, health-care professional and PHCT characteristics on the CPV of preventive services in Spain.

### Sources of information in Primary Care: the computerization of clinical records

Primary Care uses electronic clinical records (ECRs) to monitor health problems and to register preventive care services. Although information collection intends to be comprehensive, the ECR systems are different for each region.

Routinely-collected data have undisputed advantages in the study of CPV; they are available almost instantaneously and provide information on a large number of patients. The creation of registries or databases of health-care interest in PC was given a considerable boost with the computerization of clinical records. Spain, contrary to other countries [19-23], has little experience in the use of nation-wide databases containing electronic clinical records in PC. Recently, projects such as the BIFAP project in pharmacoepidemiological research [24] have been initiated in Spain.

However, there are certain difficulties in their use: 1) The data was originally collected for a function different from current research requirements; 2) ECR systems are different in each region, with different standards and computer programs; 3) The heterogeneous degree of implementation in PHCTs; and 4) The degree of exhaustivity of data recorded (for example, some activities are carried out but are not registered). Nevertheless, the potential of this type of registry has been confirmed by different European experiences mentioned earlier [25-27]. As such, the advantages associated to computerization of clinical records are beginning to be appreciated by the different regions and the richness of information provides enormous potential for the study of CPV in primary care.

### Intraclass correlation coefficient

Reports of cluster randomised studies [28] should include sample size calculations and statistical analyses that take clustering into account. The intraclass correlation coefficient (ICC) is a measure of the relatedness of clustered data [29]. Compared with individual randomisation, cluster randomisation may substantially increase the sample size required to maintain adequate statistical power [30].

One of the problems that needs to be faced in designing cluster-based studies (area or organization-based studies) is that estimates of ICC and components of variance for the outcomes of interest need to be obtained from previous studies in order to determine the required sample size for the cluster design [30-32]. There have been repeated calls for publication of ICCs for these types of studies to help others who are planning cluster-based studies [29,33-35].

The differences [30] in ICCs among potential outcome variables, the paucity of appropriate information [36] concerning components of variance or ICC and the lack of data obtained from PC settings reinforce the need for valid estimates that would ensure proper study design.

### Study objectives

The planned objectives in the present study are:

- To describe the variability in the performance of 7 preventive services (detection of smoking status and excessive alcohol consumption; screening for hypertension, obesity and hypercholesterolemia; anti-influenza and anti-tetanus immunization) in a population older than 16 years of age receiving attention in years 2006 or 2007 and to analyse factors related to their implementation.

- To analyse the evolution of 5 identified health problems (decrease in consumption or abstention from tobacco and alcohol and degree of control of hypertension, hypercholesterolemia and obesity) up to December 2008 in the population older than16 years of age attended by the reference PHCT at least once between 2006 and 2007 and followed up during 2008.

- Estimate the ICC, together with the within-cluster and between-cluster components of variance for each of the outcome measures of interest at the PC level.

## Methods/Design

### Design

This is a multi-centered cross-sectional study of a randomised sample of PHCT stratified by region to describe the variability in the implementation of 7 preventive services and their related factors in the period of 2006 or 2007. In 2008, using another cross-sectional study, the evolution or degree of control of 5 of the identified health problems will be assessed, together with the determinants of variability. We use a longer period of study because we need more time to evaluate the impact on the degree of control of these health problems due to changes on life styles.

### Setting

The study is set in PHCTs computerized prior to 1st of January 2005 in the regions of Aragón, Navarra, and Catalonia. So far computerization had occurred in 19% of 121 PHCTs in Aragón, 76% of 54 PHCTs in Navarra, and 97.5% of 278 PHCTs in Catalonia (at the Catalan Health Institute).

### Study population: PHCT and patients

We performed random cluster sampling stratified by region with computerized PHCT used as unit of randomisation.

The inclusion criteria of the PHCT are: 1) computerization of the clinical records before the 1st of January 2005 to ensure familiarity with the system's use; 2) wide use of ECR, and 3) agreement to participate in the study by most of the health-care professionals working in each PHCT (> 80%).

For each computerized PHCT we select the ECRs of all subjects older than16 years as the unit of data collection. For the assessment of variability, the ECR of subjects receiving attention at least once in each of the study years will be extracted from the database. It is estimated that the average number of subjects receiving attention per year is around 70%. Thus in a PHCT in Aragon this figure would be around 10,000 patients, in Navarra around 7,500 and in Catalonia around 12,000. For the analysis of the evolution of health problems and related factors, subjects visited at least on one occasion during the 2006–2007 period and on a further occasion in 2008 will be included.

### Sample size and randomisation

To achieve the equivalent power of a patient-randomised design, in a cluster randomised design the effective sample size will need to be the standard sample size of a single random sampling multiplied by the design effect [31,37,38]. The design effect is a function of the average cluster (computerized PHCT) size and the (intraclass correlation coefficient (ICC) of the outcome:

design effect = 1 + (n-1)*ICC

where *n *is the average number of individuals sampled per cluster [38].

sWith the cluster design we set an ICC of 0.05 on the assumption that the ICCs estimated for outcome variables from PC are less than 0.05 [28,36,39] and that the average number of individuals sampled per centre is at least of 2,500. Therefore 20 computerized PHCTs are necessary from each region to guarantee a statistical power of 80%, assuming a 50% event rate with an alpha two-tailed significance level of 0.05. Finally, to allow any of the randomised computerized PHCTs declining our offer to participate, we increased the number of computerized PHCTs selected from each region to 22. As such, the total number of subjects included will be more than 300,000 in Aragón, 200,000 in Navarra and 350,000 in Catalunya i.e. more than 850,000 subjects in total. This volume of subjects ensures a good estimate of the different outcome measures in the sub-groups of each cluster.

The selection of computerized PHCT to participate in the study is by a simple random sample within each region. Sample size calculation and computerized PHCT selection is performed with Epidat 3.1.

### Outcomes and others measures

#### Primary outcome measures

The **primary outcome measures relating to objective 1 **include the description of the implementation of preventive services according to the PAPPS criteria [6].

Screening for smoking status: if there is information on the consumption of tobacco over the last two years in members of the population who previously were non-smokers.

Screening for excessive alcohol consumption: if there is information on the consumption of alcohol over the last two years in members of the population who previously were not high consumers of alcohol.

Screening for obesity: if there have been measurements of height and weight or body mass index (BMI) over the last 4 years in members of the population who previously were non-obese.

Screening for hypertension: if there is information on systolic blood pressure (BPS) and diastolic blood pressure (BPD) during the last 4 years in members of the population aged between 16 and 40 years who previously did not have the diagnosis of hypertension; or over the past 2 years in members of the population older than 40 years who previously did not have the diagnosis of hypertension.

Screening for hypercholesterolemia: if there is information on total blood cholesterol corresponding to the following criteria of age and gender: 1 measurement in males between 16–35 years old; 1 measurement in females between 16–45 years old; 1 measurement every 5 years in males between 35–75 years old; 1 measurement every 5 years in females between 45–75 years old; 1 measurement if there has not been a previous measurement in those older than 75; all of these performed in population that previously did not have the diagnosis of hypercholesterolemia.

Anti-tetanus vaccination (ATV): if there is a registry of anti-tetanus vaccination over the previous 10 years.

Anti-influenza vaccination (AIV): if there is a registry of annual anti-influenza vaccination in those older than 59 years of age.

The **primary outcome measures relating to objective 2 **describes the clinical follow-up of the five health problems identified up to December 31^st ^2007 and evaluated up to December 31^st ^2008:

Evolution of tobacco consumption: quit smoking or remaining an ex-smoker.

Evolution of excessive alcohol consumption: cessation of consumption or decrease below the definition of excessive consumption (28 alcohol units/week in males and 17 alcohol units/week in females, where 1 alcohol unit = 10 grams of alcohol).

Evolution of obesity: decrease in BMI to <30 kg/m^2 ^or change in the diagnosis to non-obese.

Evolution of hypertension: mean of the last 2 determinations of systolic BP/diastolic BP registered as being ≤ 130/80 mmHg in patients of high risk (diagnosed with diabetes, renal or cardiac insufficiency) and ≤ 140/90 mmHg in the rest of the population.

Evolution of hypercholesterolemia: last measurement of LDL cholesterol registered as being ≤ 100 mg/dL in high-risk patients (diagnosed with diabetes, ischaemic heart disease or cerebrovascular accident) and ≤ 130 mg/dL in the rest of the population.

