#### Other measures

We assess the following factors related to the outcome measures according to the levels of analysis:

Computerized PHCT: variables of structure and organization of the PHCT (number of GPs and nurses, presence of specialists), adherence to PAPPS, training centre for family doctors, ECR system and starting year, assigned population.

Health-care professionals (GPs, nurses): gender, age, specialty, years of employment in PC and in the PHCT, workload (mean number of visits/day), years of experience with ECR.

Subjects: gender, age, comorbidity according to the Adjusted Clinical Groups grouper [40,41], frequency of consultations (visits/year).

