#### Quality control

Quality controls will be carried out in the 2 extractions of data comparing agreement between the central database and the original data of some centres as for: number of patient, visits and diagnoses as well as data of prevalence of certain diseases. It will also be checked if the population data is appropriate by comparing it with data from the census and other official sources. In the case of items related to clinical activities (for example blood pressure measurement), any register with missing values will be considered as not performed.

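### Look-back windows of 4, 5 and 10 years exceed the electronic history guaranteed for every team, so recorded implementation may be understated, and unevenly across teams, for tetanus, cholesterol, obesity and blood pressure at ages 16–40

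*Protocol article*

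**What the plan says.** Under Study population, a team is eligible on "computerization of the clinical records before the 1st of January 2005 to ensure familiarity with the system's use". The reason given is familiarity with the system; the date is not tied to any outcome window. Under Design, the first objective is "to describe the variability in the implementation of 7 preventive services and their related factors in the period of 2006 or 2007".

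Primary outcome measures sets the windows:
- Tetanus: "Anti-tetanus vaccination (ATV): if there is a registry of anti-tetanus vaccination over the previous 10 years".
- Obesity: "measurements of height and weight or body mass index (BMI) over the last 4 years".
- Blood pressure: 4 years at ages 16–40, 2 years above 40.
- Cholesterol: one measurement every 5 years in the middle age bands, and a single measurement with no stated time limit in the younger and oldest bands.
- Smoking and alcohol: 2 years. Influenza: annual.

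Information source takes patient data from the electronic record servers only. Quality control adds that, for clinical activities, "any register with missing values will be considered as not performed". Other measures lists "ECR system and starting year" among the team factors and years of ECR experience among the professional factors. Statistical analyses adjusts for factors at all three levels, but the first ICC step has random effects and no covariates.

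**The concern.** The eligibility date and the outcome windows do not fit together. A team computerised at the end of 2004 can have a complete electronic history for the 2-year and annual criteria, but not for the 4-, 5- and 10-year ones or the untimed cholesterol ones. A tetanus dose given in 2000 and never keyed in would be scored as a failure of the team rather than as unobservable. Even without the missing-value rule the outcome definition has this effect, because success means presence in the record.

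Length of record is a property of the team, so the error falls on the level that the study sets out to describe. At stake are the between-team variability and its related factors (objective 1), the ICCs offered to planners of future cluster studies (objective 3), and the secondary count of services per person, which inherits the problem. In the adjusted models, starting year and ECR experience are candidate explanatory factors. An apparent effect of either could reflect how much history can be seen, how well the team performs, or both.

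**Working it through.** The plan gives no figure of its own on this point, so there is nothing to reproduce. The inputs are:
- Latest permitted start: end-2004 (Study population).
- Assessment at end-2006 and end-2007. Design gives the years; the year-end reference date is an assumption.
- Windows W: from Primary outcome measures.
- Illustrative true coverage c: 70% for obesity, cholesterol and tetanus, and 92.8% for hypertension, borrowed from the past evaluations described in the Background (more than 70%, and 92.8% for the hypertension, smoking and alcohol group). They are not forecasts.
- Yardstick: the planning ICC of 0.05 (Sample size and randomisation).

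**Step 1. Observable share of the window.** With y years of record, the share is min(1, y/W). The latest-starting eligible team has y = 2 at end-2006 and y = 3 at end-2007.

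| Window | End-2006 | End-2007 |
|---|---|---|
| 2 years | 100% | 100% |
| 4 years | 2/4 = 50% | 3/4 = 75% |
| 5 years | 2/5 = 40% | 3/5 = 60% |
| 10 years | 2/10 = 20% | 3/10 = 30% |

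This step needs only the protocol's dates and the year-end assumption.

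**Step 2. Recorded coverage for that team if nothing was back-entered.** Two models for the timing of events: evenly spread dates, c·y/W; and constant hazard, 1 − (1 − c)^(y/W). For tetanus at end-2007: 0.70 × 3/10 = 21%, and 1 − 0.30^0.3 = 30%.

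| Service | True (assumed) | End-2006 | End-2007 |
|---|---|---|---|
| Tetanus | 70% | 14–21% | 21–30% |
| Cholesterol, 5-year bands | 70% | 28–38% | 42–51% |
| Obesity | 70% | 35–45% | 53–60% |
| Blood pressure, ages 16–40 | 92.8% | 46–73% | 70–86% |

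A team whose record spans the window would show the full 70% or 92.8%.

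**Step 3. ICC from record length alone.** Give all teams identical true performance, assume start dates uniform over the 3, 5 or 7 years before 2005 and no back-entry, and take Var(p)/[p̄(1 − p̄)] across teams. The ranges run over the three spreads and both timing models.

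| Service | End-2006 | End-2007 |
|---|---|---|
| Tetanus | 0.02–0.08 | 0.02–0.08 |
| Cholesterol, 5-year bands | 0.03–0.08 | 0.01–0.04 |
| Obesity | 0.02–0.06 | 0.002–0.012 |
| Blood pressure, ages 16–40 | 0.02–0.15 | 0.002–0.046 |

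Under these assumptions the artefact can be as large as the planning ICC for tetanus in both years. For obesity it is small by end-2007.

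**The case against.** The case on the other side has five parts.

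*Back-entry.* The criteria ask whether an event inside the window is recorded, not whether it was entered when it happened. Older doses or results keyed in or migrated later would count, and this is plausible for vaccinations. The protocol is silent. A reader might infer that recent teams look worse by construction; the documents do not support that without the added assumption of no back-entry. This objection stands.

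*Spread of starting years.* Only a latest date is given. If starts cluster, rates fall about equally and between-team variance is hardly affected. A reader might contrast the latest-starting team with one computerised on 1 January 2000: for tetanus at end-2007, 0.70 × 3/10 = 21% against 0.70 × 8/10 = 56%, a gap of 35 points. That is an extreme illustration built on an invented comparator, evenly spread dates and no back-entry. This also stands.

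*Breadth.* It is tempting to say that four of the seven services are affected throughout. Blood pressure is affected only at ages 16–40; above 40 the 2-year window is covered. Evenly spread single events also suit repeated measurements poorly. Under constant hazard, the end-2007 shortfalls are 92.8% to 86% for blood pressure and 70% to 60% for obesity.

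*Adjustment.* Starting year is collected, team-level adjustment is planned, and adjusted ICCs follow the unadjusted ones. This can absorb part of the artefact. It does not reach the descriptive rates, the cluster-level analyses or the first ICC step. A reader might call the starting-year association spurious; that goes too far, because a real effect of experience may coexist. The coefficient is confounded with record length.

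*Acknowledged limits.* The Background and Discussion concede incomplete recording and rely on system stability and quality control. Neither addresses services given before the system existed.

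**Conclusion.** The point holds as a mismatch between the eligibility date and the look-back windows. What is certain is the guaranteed history of 2 and 3 years and the resulting window shares of 50%/75%, 40%/60% and 20%/30%, given year-end assessment. The direction, downward and more so in recently computerised teams, holds unless earlier events were entered retrospectively. The size is unknown, because the extent of back-entry and the distribution of starting years are not given; the coverage and ICC figures above are ranges under stated assumptions. The descriptive variability and unadjusted ICCs may therefore be inflated for tetanus, cholesterol, obesity and blood pressure at ages 16–40, and the count of services with them. Tetanus is the most exposed. In adjusted models, a starting-year effect cannot be told apart from record length.

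**What to change.** Keep the PAPPS-window outcomes as defined. For tetanus, cholesterol, obesity and blood pressure at ages 16–40:

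1. Add a between-team comparison, factor models and ICCs on a look-back that every eligible team can supply, for example the 3 years to 31 December 2007.
2. Where enough teams have records that cover the full window, also report the PAPPS rate and ICC in those teams.
3. State that the coefficients for ECR starting year and ECR experience will not be interpreted as determinants of performance where the window exceeds the record length.

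No new data are needed, because starting year is already collected; the cost is additional analyses and some text. There are two downsides. The common-window rate is lower than the PAPPS rate and not directly comparable with it: with a 3-year window, a person vaccinated against tetanus 4 to 10 years ago meets the PAPPS criterion but fails the common-window one. And few or no teams may have records long enough for the 10-year tetanus window, in which case item 2 cannot be done for that service.
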